## Rationale for choice of method

This trial is therapeutically and diagnostically noninterventional. The procedure followed by the involved physicians is not influenced by this trial. The physician is completely free in his/her decision regarding which patients he/she treats with the medication observed in this trial, which doses he/she chooses, which diagnostic measures he/she takes, how he/she monitors the course of treatment or which concomitant or additional medication he/she prescribes. The appointments for the physician-patient contacts are determined individually. The documentation time points are scheduled.

The choice of this methodological approach in the noninterventional study necessarily follows from the subject of investigation, which is to collect scientific data reflecting the clinical routine as far as possible.

Recording of data on the course and outcome of treatment in daily medical practice can only reflect reality in a noninterventional study. The decisive criterion for this is the inclusion of a large number of gastroenterology or other specialized practices and hospital outpatient departments experienced with interferon treatment, which are deliberately not chosen to comply with the strict requirements of a clinical study and which routinely treat hepatitis C patients. Moreover, access to patients is on an open basis; data are recorded for patient populations that reflect a majority of the hepatitis C patients in Germany, but who are normally not investigated in clinical studies because of strict inclusion and exclusion criteria (e.g. addiction patients or HIV-HCV coinfected patients).

# Selection criteria

## Procedure for selection of participating physicians

Any physician providing routine treatment with peg­interferons to HCV infected patients can participate in the noninterventional study. In Germany, HCV treatment is delivered mainly in specialized practices and hospital outpatient departments. These sites are specifically chosen for the noninterventional study by the field force of Roche Pharma AG, Grenzach-Wyhlen.

It is planned to included around 600 centres in the prospective noninterventional study.

## Description of patient access

Reflecting the research subject of this noninterventional study, the members of the patient population generally suffering from chronic hepatitis C are included in this study who require medicinal treatment during therapy and for whom the treating physician takes the individual decision to provide treatment with peg­interferon alfa-2a (Pegasys®).

The treating physician is requested to document the treatment data of all patients for whom he/she takes the individual decision to perform the medicinal therapy with peg­interferon alfa-2a (Pegasys®) based on therapeutic necessity in the period from 1 January 2008 to 31 December 2011 after receiving the study documentation.

# Conduct of the noninterventional study

## Duration and premature termination of the noninterventional study

The noninterventional study will start on 1-Jan-2008 and is scheduled to end on 30-Jun-2014. The individual duration of the documentation of a patient is about 72 weeks.

The noninterventional study is intended to cover the entire treatment period (depending on the physician's decision and the main baseline factors such as genotype and viral load, or up to the end of treatment with peg­interferon alfa-2a (Pegasys®). Independently of the treatment decision taken, concluding documentation is to be generated for every patient even after discontinuation of treatment with peg­interferon alfa-2a (Pegasys®).

In the event of premature termination of the overall prospective noninterventional study, for example for regulatory reasons, the available data will be analyzed completed and a final report of the prospective noninterventional study will be compiled, if appropriate in a reduced form.

## Procedure

This trial does not influence the individual course of treatment. The noninterventional study has no influence on the medical decisions and procedures. The participating physician is requested, however, to document the decisions and measures taken in the case record form of this noninterventional study.

The documents attempt to reflect the usual course of treatment as closely as possible and thereby facilitate documentation. Under no circumstances are they to be misunderstood as instructions for the management of treatment.

The documentation procedure per patient is as follows:

1. the diagnosis is made and the treatment decision is taken outside the study
2. patient informed consent
3. patient status and statement regarding start of study
4. any interim findings
5. patient status and information on treatment at end of study. The final documentation should generally be performed 48 – 72 weeks after the start of the study or at the end of the treatment, if this is sooner.

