| Selected patient population: | Therapy data from patients over 18 years of age, with a diagnosed chronic hepatitis C with detectable virus replication and no contraindication for the use of peg (40kDa)-interferon alfa-2a (Pegasys®) or combination therapy with ribavirin (Copegus®), can be documented (please see product information).  Women of childbearing potential should use adequate contraception. It is important that female patients of childbearing potential and their sexual partners use 2 contraceptive methods at the same time during treatment and 4 months after treatment discontinuation. During this time pregnancy tests have to be performed monthly.  Particular attention is also required and pregnancy should be avoided 7 months after treatment discontinuation in female sexual partners of male patients taking ribavirin (Copegus®). Both should use adequate contraception.  Ribavirin (Copegus®) must not be used in pregnant women.  Please see the current German product information. |
| Planned number of patients: | 9000 |
| Selected physician population: | Participation is open to all physicians familiar with interferon therapy in Germany. |
| Planned number of centers: | 600 |
| Selection criteria: | Selection will take place by a specialized field force. Criteria are experience of physicians in the treatment of chronic hepatitis C and a known excellent documentation quality in the past |
| Main parameters of interest: | Demographic data, anamnesis of hepatitis C, viral genotype and viral load, relevant laboratory parameters, histology (if available), concomitant diseases, data of treatment and dosage of Peginterferon alfa-2a and ribavirin and other concomitant medication, virological outcome: RVR, EVR, EOT, SVR, (severe) adverse events |
| Procedures: | Baseline, routine visits at weeks 2, 4, 8, 12, 24, 36, 48, EOT and EoFU, additional modules for HIV-coinfection, opioid substitution, cardiovascular risk, HCV after liver transplantation, and pharmacoeconomics |

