#### To week 24 of follow-up

- Body weight
- Laboratory parameters
  GPT (=ALT), GOT (= AST), GGT,
  Other laboratory parameters:
  hemoglobin, platelets, WBC, neutrophils (%), bilirubin, creatinine, TSH, blood glucose (fasting), HbA1c, triglycerides, cholesterol, HDL, LDL, serum ferritin ANA, LKM, SMA, AMA, SLA, Trak, MAK, TSH, rheumatoid factors
- Hepatitis C laboratory diagnostic tests
  HCV-PCR (qualitative/quantitative) *only qualitative recommended*
- Hepatitis B laboratory diagnostic tests (only if chronic hepatitis B was documented at the baseline examination): HBsAg (+/-), HBeAG +/-; HBV-DNA quant./qual., anti-HBs (+/-); anti-HDV (+/-), HDV-RNA (+/-, qual. or quant.)
- Adverse events (including suspected cases) with substance-specific causality survey
- Concomitant medication
- Clinical symptoms: none, fatigue, fever, muscular stiffness, skin changes, hair loss, joint pain, muscle pain, abdominal pain, nausea, reflux, weight loss, headache, insomnia, irritability, restlessness, depression, depressive mood, psychosis, impaired concentration, anorexia, jaundice, pruritus, elevated GPT, craving / withdrawal-like symptoms, other treatment-related sick leave (duration) since the last examination
- Pregnancy
- Quality of life assessment compared to before treatment: symptom-free; improved, but not symptom-free; unchanged
- Alcohol consumption no/yes, if yes, inquiry ≤/ > 40 g/d and drinks/d in the last 30 days
- Submission of the SF-36 and sociodemography record form (questionnaire to be completed by the patient)

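### The final-documentation rule in Section 6.2 falls before the week-24 follow-up HCV-PCR for 16-, 24- and 72-week courses and for early stoppers, which contradicts the follow-up scheduled elsewhere in the protocol

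*Protocol*

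**What the plan says.** Section 6.2 lists the documentation steps per patient. Item 5 sets the final documentation, as a general rule, at 48 to "72 weeks after the start of the study or at the end of the treatment, if this is sooner". Follow-up is not mentioned.

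Section 6.1 says that "The noninterventional study is intended to cover the entire treatment period", up to the end of peginterferon treatment, and again does not name follow-up. It adds that "concluding documentation is to be generated for every patient even after discontinuation of treatment", without saying when, and that "The individual duration of the documentation of a patient is about 72 weeks".

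Other places plan for data after treatment:

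- **Synopsis:** the procedures are "Baseline, routine visits at weeks 2, 4, 8, 12, 24, 36, 48, EOT and EoFU", so end of treatment and end of follow-up are separate visits. The main parameters include "virological outcome: RVR, EVR, EOT, SVR".
- **Section 7.2.2:** the main module has its own form headed "To week 24 of follow-up", which includes an HCV-PCR. The opioid, HIV, cardiovascular and transplant modules also have a follow-up week 24.
- **Section 7.4:** adverse events are documented through the follow-up phase, but for only up to 90 days in patients who discontinue prematurely.
- **Section 8.3:** laboratory categories are compared between end of treatment and follow-up.
- **Section 11:** the week-24 follow-up visit is paid (EUR 67.02 for the main module), and the quality-of-life forms are due there too.

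**The concern.** The main objective is efficacy and safety in routine care, with a descriptive comparison against clinical-study data. Of the four virological outcomes listed, SVR is the only one that needs a sample after treatment. A centre that takes item 5 at its word has finished with a short-course patient on the day treatment ends, whereas a centre that works from the visit schedule has not. Whether SVR is known would then depend on which instruction the centre followed and on how long the patient was treated.

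End-of-treatment response cannot stand in for SVR. Section 4.1.3 itself notes that 24 weeks of treatment may carry a higher relapse risk than 48 weeks, and relapse is seen only after treatment.

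Two details make a slip more likely and harder to repair. The end-of-treatment form in Section 7.2.2 is headed as the end of treatment or of documentation, which supports the misreading. Under Section 7.1 the software does not accept dates older than three months, so a follow-up PCR that comes to light late may no longer be enterable.

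**Working it through.** **Inputs**

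- Treatment durations from the Synopsis (Duration): 16, 24, 48 and 72 weeks. They are used only to place the visits in time.
- Follow-up visit: 24 weeks after end of treatment (Section 7.2.2).
- Final documentation: Section 6.2, item 5.
- Assumption: SVR is read from the follow-up PCR. The protocol lists SVR without defining it, but this is the only PCR scheduled after treatment.

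**The plan's own figure.** Section 6.1 gives about 72 weeks per patient. Treatment of 48 weeks plus 24 weeks of follow-up gives 48 + 24 = 72, so the figure is reproduced and fits a 48-week course that includes follow-up.

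**Two readings of item 5.** The text does not say whether sooner means before week 72 or before week 48.

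- Reading A: final documentation at end of treatment whenever that precedes week 72, i.e. week min(T, 72), where T is the treatment duration in weeks.
- Reading B: final documentation at end of treatment only if T < 48; otherwise anywhere in weeks 48 to 72.

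**Comparison.** The follow-up PCR falls due at week T + 24.

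| Treatment T (weeks) | PCR due (T + 24) | Final documentation, A | Final documentation, B | Reaches the PCR? |
| --- | --- | --- | --- | --- |
| 12 (early stop, illustration) | 36 | 12 | 12 | No, 24 weeks early |
| 16 | 40 | 16 | 16 | No, 24 weeks early |
| 24 | 48 | 24 | 24 | No, 24 weeks early |
| 48 | 72 | 48 | 48 to 72 | A: no, 24 weeks early; B: only at the upper limit |
| 72 | 96 | 72 | 48 to 72 | No, at least 24 weeks early |

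The two readings differ in whether the PCR can be reached only for the 48-week course. On reading B the window for a 72-week course can even open before treatment has ended.

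**Adverse events.** The 90-day limit for premature discontinuers is 90 / 7 = 12.9 weeks, which also stops short of follow-up week 24.

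**The case against.** The strongest reply is that the design plainly includes follow-up. It appears in the visit schedule, in the main form and four additional modules, in the laboratory analysis and in the fee table. A centre would have to pass over a scheduled and paid visit to act on the literal wording of item 5. That wording is also soft (should generally), and Section 7.1 has entry confirmed form by form, with no closure at patient level. The window limits look as if they were built around follow-up, since 24 + 24 = 48 and 48 + 24 = 72 are the PCR weeks for the two standard courses in naive patients.

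Most of this stands, and it rules out stronger statements that a reader might infer:

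- **That every record is closed before SVR, so that no patient has a result.** The protocol states no lock, and a 48-week course can reach its week-72 PCR on reading B.
- **That SVR is the designated main efficacy outcome.** It is one of four virological outcomes listed together. Its weight is a fair inference, but the protocol does not rank it.
- **That a given share of the 9,000 patients will lack SVR, or that SVR will be biased by a given amount.** Nothing in the document supplies a rate.

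In addition, for patients who stop for lack of virological response the missing PCR costs little, because the Synopsis describes later success without early response in genotypes 1 and 4 as very rare (below 2%). This does not cover those who stop for tolerability, compliance or their own wish, all of which are listed reasons in Section 7.2.2.

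The reply does not remove the contradiction. The clause about end of treatment overrides the window for exactly the courses shorter than 48 weeks, and no reading of item 5 reaches the PCR of a 72-week course.

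**Conclusion.** The point holds as an internal contradiction that should be fixed. Section 6.2, item 5, and the coverage sentence in Section 6.1 cannot be followed together with the Synopsis and Sections 7.2.2, 7.4, 8.3 and 11. Item 5 falls 24 weeks before the follow-up PCR for 16- and 24-week courses and for early stoppers, and at least 24 weeks before it for 72-week courses. For 48-week courses the gap is between 0 and 24 weeks, depending on the reading and on where in the window the centre documents.

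The consequence is a risk of missing SVR that differs by centre, treatment duration and early stopping. Those groups may well differ in SVR, so the loss need not be random, but neither its amount nor the resulting bias can be derived from the document. The conclusion rests on two assumptions: that SVR is read from the week-24 follow-up PCR, and that the treatment durations are those given in the Synopsis.

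**What to change.** - **Section 6.2, item 5:** state that the final documentation is the week-24 follow-up visit, 24 weeks after the end of treatment, for every patient including early stoppers, and that the end-of-treatment form is not the final documentation. This sets when the record is completed. It does not require any test, so the noninterventional character is unchanged.
- **Section 6.1:** state that coverage includes follow-up and that individual duration is actual treatment duration plus 24 weeks: about 72 weeks for a 48-week course, up to 96 for a 72-week course, and shorter for early stoppers.
- **Section 7.4:** reconcile the 90-day adverse event limit for premature discontinuers with a final visit at follow-up week 24.
- **Study calendar:** 96 weeks after the last planned inclusion (31 December 2011) is 2 November 2013. That lies within the study end in Section 6.1 (30 June 2014) but after the last-patient-out date in the Synopsis (30 June 2013), so those two dates should be aligned as well.

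The cost is a few sentences and a notice to centres. The follow-up form, its PCR field and its fee already exist.

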# Description of nature and scope of documentation

## General structure of the case record form

Before inclusion in the noninterventional study, the patient and the participating physician sign an informed consent form (see Annex 14.1). This remains with the treating physician and is not part of the case record form.

An electronic case record form must be completed for every patient participating in the noninterventional study and must be available with an electronic signature of the physician or a person authorized by him/her. This also applies for patients in whom an initial treatment was commenced and who may have been switched to a different treatment.

Since the documentation in a noninterventional study should be prospective, the participating physician is requested to ensure that data documentation is generated as soon as possible. The software for data recording in the noninterventional study is therefore programmed so that dates older than three months are not accepted.

Patient names must not be shown on the case record form or in other documents forwarded to the sponsor.

The physician or a person authorized by him/her receives a user name and a password for access to enter data into online electronic case record forms. Entry is completed and confirmed by the corresponding confirmation at the end of each case record form.

All information recorded in the noninterventional study is confidential. If the participating physician makes the records of the noninterventional study accessible to a third party or transfers them to a different location, Roche Pharma AG, Grenzach-Wyhlen is to be informed in writing in advance.

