# Reimbursement and fees

Reflecting the nature of the noninterventional study (observational study), the costs of the prescribed product and the medical services are reimbursed by the usual funding agencies as part of routine treatment. The fee for the noninterventional study is therefore to be understood exclusively as reimbursement for recording of the data. The complete documentation of the treatment data of a patient who can be documented in all modules based on the severity of his/her disease is reimbursed with 1,695.34 Euros. The fee can only be paid if the data made available are evaluable under the terms of this observational protocol.

The basis for calculation are reimbursement codes 80 and 85 of the Statutory Scale of Fees for Physicians; code 80 (EUR 17.49) is applied for a documentation effort of up to 20 minutes, whereas from a time input of 20 minutes onwards, reimbursement code 85 (EUR 29.14 for every started hour) applies. An increase factor of up to 2.3 can be applied to the codes depending on the estimated time required for the documentation.

The total amount for the complete documentation of a patient is calculated by adding up the complete documentation for the various visits in the main module hepatitis and the respective secondary modules HIV coinfection, opioid substitution, cardiovascular risk, liver transplantation and pharmacoeconomics. The assessment of the individual visits is shown in the following table.

| Module | Hepatitis | GÖA* | Factor | HIV infec-tion | GOÄ | Fac-tor | Opioid sub-stitution | GOÄ | Fac-tor | Cardio­vascular risk | GOÄ | Fac-tor | Trans­plan­ta­tion | GOÄ | Factor | Pharma­co-economics | GOÄ | Factor |
| --- | --- | --- | --- | --- | --- | --- | --- | --- | --- | --- | --- | --- | --- | --- | --- | --- | --- | --- |
| Baseline examination | 67.02 | 85 | 2.3 | 67.02 | 85 | 2.3 | 34.98 | 80 | 2 | 20.11 | 80 | 1.15 | 67.02 | 85 | 23 |  |  |  |
| Week 2 | 29.73 | 80 | 1.7 |  |  |  | 127.49 | 80 | 1 |  |  |  |  |  |  | 22.74 | 80 | 1.3 |
| Week 4 | 34.98 | 80 | 2 |  |  |  | 127.49 | 80 | 1 |  |  |  |  |  |  | 22.74 | 80 | 1.3 |
| Week 8 | 34.98 | 80 | 2 |  |  |  | 127.49 | 80 | 1 |  |  |  |  |  |  | 22.74 | 80 | 1.3 |
| Week 12 | 58.28 | 85 | 2 | 34.98 | 80 | 2 | 17.49 | 80 | 1 |  |  |  | 58.28 | 85 | 2 | 22.74 | 80 | 1.3 |
| Week 24 | 58.28 | 85 | 2 | 34.98 | 80 | 2 | 24.49 | 80 | 1.4 | 20.11 | 80 | 1.15 | 58.28 | 85 | 2 | 22.74 | 80 | 1.3 |

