| Week 36 | 58.28 | 85 | 2 |  | 80 | 2 | 17.49 | 80 | 1 |  |  |  | 58.28 | 85 | 2 | 22.74 | 80 | 1.3 |
| Week 48 | 58.28 | 85 | 2 | 34.98 | 80 | 2 | 24.49 | 80 | 1.4 | 20.11 | 80 | 1.15 | 58.28 | 85 | 2 |  |  |  |
| End of treatment | 67.02 | 85 | 2.3 | 34.98 | 80 | 2 | 24.49 | 80 | 1.4 | 20.11 | 80 | 1.15 | 58.28 | 85 | 2 | 22.74 | 80 | 1.3 |
| W24 follow-up | 67.02 | 85 | 2.3 | 34.98 | 80 | 2 | 24.49 | 80 | 1.4 | 20.11 | 80 | 1.15 | 58.28 | 85 | 2 | 22.74 | 80 | 1.3 |
| **Total** | **533.88** |  |  | **241.92** |  |  | **220.37** |  |  | **100.57** |  |  | **416.70** |  |  | **181.90** |  |  |
| **Max. total per  patient** | **1695.34** |  |  |  |  |  |  |  |  |  |  |  |  |  |  |  |  |  |

* German Scale of Statutory Fees for Physicians

For incompletely documented visits that cannot be used for the evaluation under the terms of the observational protocol, relevant queries are submitted to the participating physicians through the query management that make it possible to fully present and complete the visits. If no complete documentation of a visit is achieved, the documentation is not reimbursed.

Since on the one hand prompt documentation is required and on the other hand it is usually impossible to document data electronically during a patient visit in addition to maintaining the patient file, it is advisable first to document the data in a hardcopy version of the case record form and then to transfer this version to the electronic CRF later on. Transfer to the electronic CRF can be delegated by the participating physician to a study assistant. The contracting party can contractually assign 20 % of the documentation fee to the study assistant for this purpose. 80 % of the total fee amount then remains for the contracting party. (For administrative reasons, agreement to a change in the percentage distribution between the contracting party and the study assistant is only granted in justified exceptional cases and after the agreement of the medical manager or one of his representatives.)

For the documentation of the prescribed HIV concomitant medication in the pharmacoeconomics part, a documentation effort of EUR 34.98 is reimbursed with a factor of 2 in accordance with the statutory fees for physicians.

For the documentation of the prescribed substitution medication in the pharmacoeconomics part, a documentation effort of EUR 17.49 is reimbursed with a factor of 1 in accordance with the statutory fees for physicians.

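### The three-month eCRF date lock does not secure inclusion before early response is known, and read literally it refuses some non-serious post-treatment adverse events

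*Protocol*

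**What the plan says.** Section 7.1 states both the aim and the tool. It begins "Since the documentation in a noninterventional study should be prospective", asks the physician to document as soon as possible, and for that reason has the software "programmed so that dates older than three months are not accepted". It names no exception and does not say which date fields the check covers.

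On the timing of inclusion:
- Section 7.1: "Before inclusion in the noninterventional study, the patient and the participating physician sign an informed consent form".
- Section 6.2 sets the order of steps. First "the diagnosis is made and the treatment decision is taken outside the study", then consent, then status at the start of the study, then interim findings. No step has a deadline.
- Section 5.2: "The treating physician is requested to document the treatment data of all patients" for whom the treatment decision falls between 1 January 2008 and 31 December 2011.
- Section 7.2.2, baseline, records the consent date and the start of treatment, and lists an SF-36 form to be completed ahead of therapy.
- Section 11: "it is advisable first to document the data in a hardcopy version of the case record form", with transfer to the eCRF afterwards. The same sentence acknowledges that documentation has to be prompt.

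On what is collected, and when:
- Section 7.2.2 recommends HCV-PCR at weeks 4 and 12. After end of treatment its only visit is the one headed "To week 24 of follow-up".
- Section 7.4 asks for all adverse events, serious or not, through follow-up. After premature discontinuation it asks for them for up to 90 days.
- The Contact page and Section 7.5 require serious and expedited events within 24 h.

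**The concern.** The lock is the only programmed safeguard for prospective documentation. A window of about three months is much longer than the four weeks to the first virological result. A centre can therefore decide whether to enter a patient after seeing RVR and how the first weeks were tolerated. If early failures and early dropouts are entered less often, RVR, EVR and SVR come out too high and intolerance too low. Those are the two halves of the main objective, and they are to be compared descriptively with clinical-study data. Section 8.1 assumes a representative sample, and 9,000 patients do not average out a selection effect. Source-data checking (Section 10.3.1) compares documented patients with their files, so it cannot reveal patients who were never entered. The fee rule does not counteract the selection either: "The fee can only be paid if the data made available are evaluable", and Section 11 pays by completely documented visit, so an early dropout earns the centre less.

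At the other end, a rule meant to enforce timeliness may turn away genuine events. The interval from end of treatment to the follow-up visit is longer than the lock, and non-serious events count in the tolerability tables of Section 8.3.

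**Working it through.** The protocol gives no figure to reproduce. The check is calendar arithmetic plus a comparison of the inclusion rules.

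**Step 1. Length of the lock.** Subtracting three calendar months from every possible entry date between 1 January 2008 and 30 June 2014 (Section 6.1) gives L = 89 to 92 days, or 12.7 to 13.1 weeks.

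**Step 2. First entry after an early result.** Take treatment start as the oldest date to be accepted. The slack after the week-w sample is L − 7w.
- Week 4 (day 28, RVR): 89 − 28 = 61 to 92 − 28 = 64 days.
- Week 12 (day 84, EVR): 89 − 84 = 5 to 92 − 84 = 8 days.

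The week-4 result can be known with about two months to spare. The week-12 result can be known only if the laboratory reports within 5–8 days, and only if no locked baseline date lies further before the first dose than the days left. Turnaround is not given in the protocol.

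**Step 3. Does another rule close the gap?**
- Consent must precede inclusion (7.1), but inclusion is not tied to the first dose.
- Consent follows a treatment decision made outside the study (6.2), with no time limit.
- Documentation of all treated patients is a request (5.2), and no screening log is described.
- The pre-therapy SF-36 (7.2.2) is listed, but it is not a condition of entry.

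None of these requires consent or first entry before the first dose or before the week-4 PCR.

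**Step 4. Adverse events first entered at follow-up week 24.** The gap is G = 24 × 7 = 168 days. Onsets refused under a literal reading fall in the first G − L days.
- 168 − 92 = 76 to 168 − 89 = 79 days, about 11 weeks.
- Share of the gap: 76/168 = 45% to 79/168 = 47%. This is a share of days, not of events.
- Share of the 90-day window after premature discontinuation: 76/90 = 84% to 79/90 = 88%.
- The 12-week on-treatment gaps (84 days) are shorter than 89 days, so nothing is refused there.

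**Step 5. SVR date.** The SVR sample belongs to the follow-up visit, so at that visit its date is 0 days old. It is refused only if entered more than 89–92 days after the test.

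**Step 6. Illustrative size of the selection effect.** Every input here is an assumption. Let true SVR be 50%, let a fraction a of patients be open to late entry, let a fraction b of those never be entered, and let all omitted patients be non-SVR. Then observed SVR = 0.50 / (1 − a·b).
- a = 0.20, b = 0.10: 0.50/0.980 = 51.0%
- a = 0.30, b = 0.15: 0.50/0.955 = 52.4%
- a = 0.50, b = 0.25: 0.50/0.875 = 57.1%
- a·b = 0: 50%, no bias

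For scale, the 95% sampling half-width at n = 9,000 is 1.96 × √(0.25/9000) = 1.0 point.

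**The case against.** Several counter-arguments have force.

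- **Late transfer is not late inclusion.** A patient who consented and was documented on paper before therapy, then keyed in later, was not selected on response. Section 6.2 puts consent ahead of the start-of-study status, and Section 5.2 asks for everyone treated. This stands. It makes consent date, not eCRF entry date, the right marker. It does not close the gap, because nothing places consent before the first dose.
- **The lock cannot cover every date.** The form asks for histology, first antiretroviral treatment and transplantation dates, which will often be older than three months. A check on visit dates alone is a plausible reading, and then no adverse-event onset is refused. Events also have their own eCRF sheet and need not wait for the visit. This stands as a limit: the adverse-event point holds only under the literal reading, and the protocol should state the scope.
- **Recruitment is over.** This version is dated 28 February 2013, and planned last patient in was 31 December 2011. A new registration gate would apply to nobody. This stands. The remedy for inclusion has to lie in the analysis.
- **The bias figures have no source.** This also stands. They restate their inputs.

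A reader might infer that the 24-week follow-up gap blocks the SVR result. It does not (step 5). Refusal needs entry more than three months after the test, which is ordinary late documentation. A reader might also infer that EVR is routinely known at first entry. The 5–8 day margin does not support that.

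**Conclusion.** The concern holds in a limited form. The lock does not achieve its stated purpose. First entry remains possible 61–64 days after the week-4 sample, and no other provision requires consent or entry before the first dose. The week-12 result is within reach only by 5–8 days and depends on a turnaround the protocol does not state.

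Under the literal reading, the lock also conflicts with Section 7.4. Non-serious onsets in the first 76–79 of 168 days after treatment would be refused if first entered at follow-up week 24. Serious and expedited events are unaffected if the 24 h rule is followed.

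The documents do not show that selective entry occurred or that events were lost. The range of 1 to 7 points on SVR is a scenario, not an estimate. It rests on assumed fractions and on every omitted patient being non-SVR, and the true effect could be zero. The point merits action because it touches both main outcomes and the remedy is cheap.

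**What to change.** 1. **Scope of the lock.** State in Section 7.1 that it applies to visit dates. Accept adverse-event onset dates and PCR result dates of any age, with an automatic late-entry flag. This can still matter: a patient starting on 31 December 2011 and treated for 48 weeks reaches follow-up week 24 after 72 weeks (504 days), in May 2013, after the date of this version.
2. **Analysis by consent date.** Classify patients by consent date relative to treatment start and to the week-4 sample. Consent date and treatment start are already collected. Present RVR, EVR, SVR and early discontinuation for those consented before treatment start, or at the latest before the week-4 PCR, next to all patients. This serves the checks of representativeness and interfering variables that Section 9 already promises.
3. **No exclusion for late keying.** Do not drop a patient from the prospectively consented set only because paper data reached the eCRF late.

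The cost is a change to one eCRF check, one additional stratified table and a smaller n in the prospectively consented set. No new data are needed. The split cannot recover patients who were never entered, but it shows whether results differ where selection on early response was possible.
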